## Abstract

**Purpose:**

Improving glycaemic control in type 2 diabetes (T2D) is essential to reducing social and health-economic burden of diabetes-related complications. Continuous glucose monitoring (CGM) has been established as beneficial in improving glycaemic control and reducing hypoglycaemia in people with type 1 diabetes, however data in T2D is limited. This study has been designed to assess the effect of initiating real-time CGM (rtCGM) on glycaemic control in a high-risk population of adults with T2D. Secondary objectives are to assess the cost-effectiveness and safety of rtCGM, and the effects of rtCGM on diet/lifestyle and the burden of diabetic complications, including cardiovascular risk.

**Methods:**

This multicentre randomised controlled trial (RCT) will be conducted at three sites in New Zealand (Waikato, Christchurch and Dunedin). Eighty adults with T2D on insulin with suboptimal glycaemic control (HbA1c > 8.0% or 64 mmol/mol) will be randomised 1:1 to rtCGM or routine care with self-monitoring of blood glucose levels (SMBG) for three months. This intervention phase will be followed by a three-month continuation phase where SMBG group crossover to use rtCGM. Participants will then be invited to join the extension phase with continued use of rtCGM for a further 12 months. During the extension phase, both groups will independently titrate their insulin under the remote supervision of prescribing diabetes nurse specialists following an insulin titration algorithm. The primary outcome of the study is time in target glucose range (3.9–10 mmol/L or 70–180 mg/dL; TIR). Secondary outcomes include CGM metrics as per consensus statement recommendations, and HbA1c. Additional planned analyses include cardiovascular risk profile, incremental cost-effectiveness analyses, dietary patterns, and qualitative analyses.

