### Randomisation

The 2GO-CGM participants will be randomly allocated to use Dexcom G6 CGM or routine care with CareSens Premier meter with an allocation ratio of 1:1. The study statistician will prepare a computer-generated randomisation list with permutated blocks of random size.

The randomisation list will be stratified by:Use of metformin (Yes/No)Use of SGLTi or GLP agonist (Yes/No)

Use of this stratification plan is based on recent public funding for SGLTi and GLP agonists as second-line agents in New Zealand. Given this recent change these agents have not been widely used and therefore participants will be randomised based on prior use of either agent on entry to the study.

The randomisation list will be loaded into the REDCap (Research Data Capture) database by the study statistician immediately prior to moving the project to production status. Once the project is moved to production, the randomisation list is locked and becomes unmodifiable and inaccessible to the study team, thereby preserving allocation concealment. The study statistician will not be involved in participant enrolment. Patients who give consent for participation, meet the eligibility criteria, and are enrolled in the study, will be given a unique study identifier. After stratification variables have been entered into REDCap, research staff with authorisation to randomise participants may click the ‘randomise’ button, which will assign the treatment to the study number according to the next allocation on the randomisation list. This process will lock the fields containing the treatment group and stratification variables. Blinding will not be possible due to the nature of the technology.

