## Glycaemic and cardiovascular risk management

Participants from all localities will be supported by prescribing DNS based at the Waikato study site, with endocrinologist support if required. For all participants, regardless of randomisation, the prescribing DNS will assist participants to manage dietary and lifestyle factors as well as medications, with a focus on participant self-adjustment of insulin during the RCT and continuation phases. Prescribing DNS will follow an insulin titration algorithm (Appendix) to ensure participants receive standardised insulin adjustment advice based on available glucose data. The prescribing DNS will make medication, diet and lifestyle recommendations (as required) at all clinic visits and remote reviews. Medication recommendations will occur as follows:

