A strength of our study design is the model of care provision alongside available glucose testing modalities. To our knowledge, this is the first RCT study investigating the use of rtCGM alongside supported specialist care with a focus on participant self-titration of insulin. Previous studies reporting improvements in glycaemic control using CGM have simultaneously observed only modest adjustments to glucose-lowering therapies in both CGM and control groups [25–27, 42]. Participants in these studies accessed care from their usual care providers during the trial phase. Type 2 diabetes is largely managed in primary care in New Zealand, and while heavily subsidised, the costs associated with visiting a primary care clinician remains a barrier to accessing diabetes care [43, 44]. Furthermore, diabetes specialists may be less prone to clinical inertia than primary care clinicians [45], particularly when specialist care adheres to clinical guidelines [46]. Our study design includes equitable, face-to-face and remote access to prescribing DNS for all study participants, with endocrinologist support for DNS as required. Prescribing DNS will assist participants to make changes to their lifestyle and medication regimens to reduce cardiovascular risk. Prescribing DNS will also support participants in both arms of the trial to self-titrate insulin doses between scheduled study review points. This self-titration education will follow an insulin titration guideline (Appendix) to reduce clinician-mediated inertia and bias in regimen changes between study groups. Bias will also be reduced by optimising non-insulin glucose lowering therapies in the run-in phase before participant randomisation.

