A further strength of our study design is the continuous and extensive use of rtCGM. Evidence from other studies using CGM in T2D suggests that the length of CGM system use influences glycaemic outcomes. RCT data from studies by Vigersky et al. [26] and Ernhardt et al. [27] showed that participants who used rtCGM for ≥48 days had greater reductions in Hba1c than those who used rtCGM for <48 days (14 mmol/mol/1.3% versus 9 mmol/mol/0.8% [26] and 13 mmol/mol/1.2% versus 7 mmol/mol/0.6% [27]). Our participants will use rtCGM continuously for 12–24 weeks according to randomisation at baseline. As such, with long duration of rtCGM use alongside supported specialist care and participant self-titration of insulin, we expect glycaemic reductions in this group to be greater than previously reported in rtCGM studies of people with T2D.

We also aim to address other deficits in literature including a paucity of qualitative data from indigenous people with T2D using technology, the effect of rtCGM use on dietary and sleep behaviours and cost-benefit analysis of technology use in high-risk indigenous populations with T2D.

The 2GO-CGM trial is likely to afford participants immediate and long-term benefits. We expect that rtCGM use will be well tolerated, and result in a cost-effective increase in TIR, and decrease in hyperglycaemia, without corresponding increase in hypoglycaemia. Our novel, integrated, remote model of care utilising prescribing DNS with endocrinologist support is likely to be effective in improving glycaemic control and cardiovascular risk in both the rtCGM and SMBG groups, as well as offer a transferable solution to real-world clinical care in the face of increasing challenges in workforce shortage and accessibility of care for people with diabetes. As such, we expect the 2GO-CGM study will provide robust evidence-based and scalable solutions for improving care for high-risk Māori and non-Māori with T2D in New Zealand and worldwide.

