### For participants on basal bolus regimen

- In addition to the above monitoring, participants in the control group should also check their glucose levels two hours after meals (i.e., 2 hours after bolus insulin administered)
- If 2-hour post-meal glucose level is >3 mmol/L than pre-meal glucose level on 3 consecutive occasions then increase dose of rapid acting insulin by 2 units at applicable meal (i.e. can increase dose every 3 days if monitoring available)
- Stop uptitration of rapid acting insulin if any of the following occurs:
  - Glucose levels <4 mmol/L at any time of day
  - Post-meal rise in glucose levels is <3 mmol/L
- At next study visit, if glucose levels at other times of day consistently >10 mmol/L consider:
  - Increasing the dose of basal insulin as per above if glucose levels increase overnight
  - Adding rapid acting insulin with snacks
  - Adding correction insulin for hyerglycaemia

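### The comparator is labelled routine care, but the trial estimates rtCGM versus SMBG inside a nurse-led titration programme that both arms receive

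*Protocol article*

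**What the plan says.** **The label.** The abstract says that participants "will be randomised 1:1 to rtCGM or routine care with self-monitoring of blood glucose levels (SMBG) for three months". The Randomisation section says that they are "randomly allocated to use Dexcom G6 CGM or routine care with CareSens Premier meter with an allocation ratio of 1:1". The Study design section also describes controls as initially randomised to routine care. The abstract mentions nurse-supervised, algorithm-based titration only for the 12-month extension phase.

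**The care described in the body.** The section on glycaemic and cardiovascular risk management states: "For all participants, regardless of randomisation, the prescribing DNS will assist participants to manage dietary and lifestyle factors as well as medications". It continues: "Prescribing DNS will follow an insulin titration algorithm (Appendix) to ensure participants receive standardised insulin adjustment advice based on available glucose data". The sections on blinded rtCGM and the run-in phase have the nurses maximise non-insulin glucose-lowering drugs for everyone before randomisation. The section on the randomised phase adds written titration instructions to follow between reviews. The control-arm section adds a Bluetooth meter, training, and sharing of glucose data with staff before review points. The Appendix sets a testing schedule for controls; on basal bolus, for example, "participants in the control group should also check their glucose levels two hours after meals".

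**How the article places this care.** Of earlier CGM trials the Discussion says: "Participants in these studies accessed care from their usual care providers during the trial phase". It offers the trial's specialist support as a contrast to that, and expects that the nurse-led model "is likely to be effective in improving glycaemic control and cardiovascular risk in both the rtCGM and SMBG groups".

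**The concern.** The same package cannot be both routine care and a novel model of care. The label matters in three places.

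- **The headline result.** Someone who reads only the abstract will take the week-12 difference as rtCGM against ordinary care, and will think that nurse-led titration began only in the extension phase.
- **The cost per percentage point of TIR.** The Health Economic Analysis section starts from the total cost of the trial less evaluation costs, and names no comparator. If the abstract's label is carried over, programme costs that both arms incur could be charged against an effect due to the monitoring method alone.
- **The care model.** The Discussion expects the model to work in both groups and to be transferable. Every participant receives it, so that claim would rest on change from baseline without a control, in people selected for HbA1c above 8.0%.

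**Working it through.** **1. Label against content, for controls in the randomised phase**

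| Element | Given to controls? | Where stated |
|---|---|---|
| Non-insulin drugs maximised before randomisation | Yes, all participants | Blinded rtCGM; Run-in phase |
| Prescribing-nurse support | Yes, regardless of arm | Glycaemic and cardiovascular risk management |
| Standard titration algorithm | Yes | Same section; Appendix |
| Written self-titration instructions | Yes | Randomised controlled trial phase |
| Remote reviews at weeks 2 and 8 | Yes | Table 1 |
| Fixed SMBG schedule | Yes, controls only | Appendix |

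Against this, the Discussion says that type 2 diabetes in New Zealand is mostly managed in primary care with a cost barrier, and the Background says that adherence to SMBG is often low.

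**2. Scheduled tests per day, from the Appendix.** Assumptions: three meals a day, and the additional tests are added to the basic schedule of before meals and bed.

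- Basal only: 3 + 1 = 4
- Basal plus: 4 + 1 = 5
- Once-daily premix: 4 + 1 = 5
- Twice-daily premix: 4 + 2 = 6
- Basal bolus: 4 + 3 = 7

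These are scheduled tests, not achieved ones.

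**3. What the randomised contrast identifies.** Write P for the effect of the programme with SMBG over true routine care, and A for the further effect of rtCGM within the programme. Relative to routine care, the rtCGM arm's mean is P + A and the control arm's is P. The trial estimates (P + A) − P = A. The effect against routine care is P + A, and the effect of the care model is P. Neither can be obtained from the randomised comparison. Change from baseline in the control arm mixes P with regression to the mean and time effects.

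**4. Costs.** Per participant, let p be the programme cost, d the rtCGM cost and s the SMBG cost. With the comparator that the trial has, incremental cost is (d + p) − (s + p) = d − s, and p cancels. The matching ratio is (d − s)/A. If the comparator were taken as routine care without the programme, the numerator would gain p while the denominator stayed at A, so cost per point would be overstated by p/A. The article gives no costs, so this has no size.

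**5. The plan's own sample-size figures reproduce.**

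- n per arm = 2 × (1.960 + 0.842)² × 20²/14² = 32.04, rounded up to 33, as stated.
- Baseline-adjusted SD = 20 × √(1 − 0.58²) = 16.29. Power for 10 points at 40 per arm = Φ(10/(16.29 × √(2/40)) − 1.96) = 78%, as stated.

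The 14 points (56% to 70%) are a between-arm difference only if controls stay at 56%. As a sensitivity range (assumption: rtCGM reaches 70% and controls gain x points):

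| x | Difference | Power, unadjusted, 33 per arm | Power, baseline-adjusted, 40 per arm |
|---|---|---|---|
| 0 | 14 | 81% | 97% |
| 2 | 12 | 68% | 91% |
| 4 | 10 | 53% | 78% |
| 6 | 8 | 37% | 59% |
| 8 | 6 | 23% | 38% |

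The range shows why it matters to name an active comparator as active. It does not show an error in the calculation.

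**The case against.** The strongest reply is that the design does what the trial set out to do. The stated purpose is the effect of initiating rtCGM, and the primary objective compares the two arms. Equal support in both arms isolates the monitoring method. This stands in full.

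The comparator is also disclosed. The body heads the arm as SMBG, the mixed model codes treatment as CGM or SMBG, and the Discussion openly presents the shared support as a strength. This stands for a reader of the whole article. It does not help a reader of the abstract, which places nurse-supervised titration in the extension phase only.

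The label may be meant to describe only the monitoring: the CareSens meter is the funded standard, and the algorithm comes from national guidelines. That makes the label understandable. But taking an algorithm from a guideline does not make nurse-delivered, protocolised titration routine, and the article itself says that usual care differs.

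Finally, the care model is not a stated primary or secondary objective, and participants' experience of it is studied through interviews. This also stands: the Discussion voices an expectation, and no planned analysis claims to prove it.

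A reader might go further and infer that the trial cannot conclude anything, that it is underpowered, or that cost per TIR point is wrong by the ratio of two effect sizes. The documents support none of these. The contrast within the programme is sound. They give no expected control-arm gain, and the protocol's own 10-point case keeps 78% power with no loss to follow-up. A ratio of effects holds incremental cost fixed while the comparator changes, which it would not be; without cost figures neither size nor direction is known.

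**Conclusion.** The concern holds as a defect of labelling and interpretation. The name routine care, used in the abstract, Study design and Randomisation sections, does not match the care that controls receive. The week-12 estimate is the add-on effect of rtCGM over SMBG within a shared nurse-led titration programme. It is not the effect of rtCGM against routine care, and there is no controlled estimate of what the care model does.

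The primary comparison, its analysis and the stated sample-size figures are unaffected. The 4 to 7 scheduled tests a day rest on three meals and on adding the extra tests to the basic schedule. The consequence for cost-effectiveness depends on which comparator the analysts adopt and cannot be sized from the article. The wording should be corrected before results are reported.

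**What to change.** - **Abstract, Study design and Randomisation:** replace the routine-care label with SMBG with the same nurse-supported protocolised titration. Say in the abstract that this support applies to both arms during the randomised phase.
- **Health Economic Analysis:** name that same comparator, so that incremental cost is the difference between arms and excludes programme costs common to both.
- **Discussion:** state that before-after change in either arm is descriptive and is not evidence that the care model works.

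These are wording changes only. No endpoint, randomisation step, model or sample size is touched. The price is a narrower headline: the trial reports what rtCGM adds within specialist-supported titration, and makes no claim against routine care.

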**Trial registration number:**

The trial was registered with the Australian New Zealand Clinical Trials Registry (ACTRN12621000889853) on 8 July 2021 and the World Health Organisation International Clinical Trial Registry Platform (Universal Trial Number U1111–1264-5822).

## Background

Treating to glycaemic target is well established as imperative to reducing diabetes-related complications [1]. However, achieving and maintaining glycaemic control in T2D remains a challenge. Despite developments in glucose lowering therapies and evolving clinical guidance in T2D management, at least 50 % of people with T2D are not achieving glycaemic targets [2–4]. Moreover, indigenous populations are less likely to achieve glycaemic targets, and experience a higher incidence and earlier onset of complications and mortality when compared to their non-indigenous counterparts [5–8]. The existence of these trends in the context of increasing health expenditure commands new approaches to improving glycaemic outcomes.

While reasons for poor glycaemic control are complex and multifactorial [9, 10], a paucity of self-monitoring of blood glucose is a significant barrier to improved diabetes management [10–12]. Self-monitoring of blood glucose (SMBG) remains an integral component of glycemic management for people using insulin [13]. Unfortunately, adherence to SMBG is often low due to the discomfort of finger pricks and the intrusive nature of the testing regimen to daily life [10, 11]. Without sufficient glucose monitoring, self-management and supported management of hyperglycaemia is impeded [14–16]. These barriers are significantly reduced in type 1 diabetes (T1D) with the use of CGM [17] and as such, CGM may offer a solution to delays in intensification of glycaemic management in T2D.

Real-time CGM (rtCGM) measures interstitial glucose levels and automatically sends glucose values via Bluetooth to a receiving device (e.g., smartphone or insulin pump), usually every 5 minutes. The CGM sensors are inserted by the user every 7–14 days (device dependant). The device also reports on glucose trends and rate of change and allows the user to set and respond to individualised alerts for low, predicted-low, high and rapidly changing glucose levels.

Real-time CGM has been shown to improve glucose control and reduce hypoglycaemia in T1D [17–22] and has become a standard of care [13, 23, 24]. Older generation rtCGM has largely demonstrated favourable outcomes in adults with T2D on insulin who are not reaching their glycaemic targets [25–29], but high-quality data of CGM use in T2D is limited. Further, there is a lack of contemporary data using modern rtCGM, which is more accurate and does not require finger prick glucose calibration. Therefore, modern rtCGM has a greater potential to be utilised by people with T2D to improve glycaemic outcomes.

Therefore, we aim to study the impact of rtCGM on a population of people with T2D at high risk of developing complications using a variety of outcome measures including glycaemic metrics, cardiovascular risk outcomes (e.g. blood pressure, HsCRP, lipids, urinary albumin:creatinine ratio), quality of life, and cost effectiveness.

## Methods

### Study design

This multi-centre, randomised controlled trial (RCT) of 80 participants will be conducted in Aotearoa New Zealand over a period of 14 weeks, including a 2-week run-in period for blinded CGM data to be collected from all participants. Following the 2-week run-in period, participants will be randomised 1:1 to either the rtCGM intervention arm (Dexcom G6 rtCGM system (Dexcom Inc., San Diego, CA)) or the control arm (SMBG) with a CareSens premier meter (i-SENS Inc., Seoul, Korea)) for a period of 12 weeks. The primary endpoint will be measured in the final two weeks of the RCT phase (week 10–12), with blinded rtCGM data collected from the control group and compared with unblinded rtCGM data from the intervention group. The 12-week RCT phase will be followed by a continuation phase, where those initially randomised to routine care will cross over into the rtCGM intervention for a further 12 weeks. Following this, participants will be invited to join the extension phase of this study and continue rtCGM use for a further 12 months. As such, the expected duration of subject participation is 78 weeks. At least five visits to the study centre and six ‘remote reviews’ are planned for participants over the study duration (see Table 1). During the 12-month extension phase participants will switch from using the Dexcom G6 system to the Dexcom G7 system, once available.

**Table 1 Tab1:** 2GO-CGM study schedule of assessments

	Baseline	Run-in period 14 days	Treatment period week 1–12				Continuation PERIOD Week 12–24			EXTENSION PERIOD Week 25–77			
	Clinic visit		Clinic visit day 1	Remote review week 2, 8	Week 10–12	Clinic visit end of study week 12	Clinic visit week 12	Remote review week 14, 20	Clinic visit end of study week 24	Week 38 remote review	Clinic visit week 51	Week 64 remote review	Clinic visit end of extension study week 77
Informed consent	X								X				
Demographics	X												
HbA1c Height, weight, BMI	X		X			X	X		X		X		X
Medical review	X					X	X		X		X		X
Blood pressure	X					X	X		X		X		X
Urine pregnancy test	X												
Fasting lipids, FBC, glucose, LFTS, eGFR	X					X	X		X		X		X
Urine ACR	X					X	X		X		X		X
Blinded CGM (14 days)		X			X (control arm)								
Return to clinic after 7 days of blinded CGM for new sensor		X			X (control arm)								
CGM training			X				X						
Electronic review				X				X		X		X	
AE collection		X	X	X		X	X	X	X	X	X	X	X
Sleep quality		X				X							
Food diary		X				X					X		
Qualitative interview						X (CGM arm)			X (control arm)			X (if used both G6 and G7 CGM)	
Retinal scan results	X												

The study protocol was approved by the New Zealand Health and Disability Ethics Committee prior to study commencement (21/CEN/75).

